### Objectives {7}

The primary objective is to examine the effectiveness of parental and systemic components that complement an intensive trauma treatment for children who have been exposed to family violence in the family. This objective translates into the following research question:
Does intensive trauma therapy for children with a family-based component (FITT) lead to a stronger reduction of trauma symptoms of children and a stronger increase of structural emotional safety than intensive trauma therapy without a family-based component (ITT)?

In addition, secondary objectives regard the elucidation of the intervention mechanism and effects on secondary outcomes. These objectives lead to the following research questions:
Does intensive trauma therapy for children with a family-based component (FITT) lead to faster reduction of trauma symptoms and increase of structural emotional safety than low-frequency trauma treatment with parent therapy and family sessions (TAU)?
After 4 weeks of treatment, does intensive trauma therapy for children with a family-based component (FITT) lead to a stronger reduction of trauma symptoms and a stronger increase of structural emotional safety than low-frequency trauma treatment with parent therapy and family sessions (TAU)?After the end of treatment, does intensive trauma therapy for children with a family-based component (FITT) lead to an equal reduction of trauma symptoms and an equal increase of structural emotional safety as in low-frequency trauma treatment with parent therapy and family sessions (TAU)?At the end of treatment, to what extent do we find the differences between intensive trauma therapy for children with a family-based component (FITT) and intensive trauma therapy without this family-based component (ITT) in trauma-informed parenting?

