### Trial design {8}

This multicentre study is a parallel-group, randomized controlled component trial to examine (1) the addition of a component with parenting therapy and family sessions to an intensive trauma-focused therapy component and (2) the addition of an intensive component to a low-frequent trauma-focused therapy with parenting therapy and family sessions. This study is a superiority trial comparing FITT and TAU after 4 weeks of treatment and FITT and ITT at end of treatment and follow-up. The comparison between FITT and TAU at follow-up concerns an equivalence trial. This randomized controlled design includes follow-up with 96 (completer’s rate 80%) children and their caregiver(s) divided over two intensive trauma treatment arms and one treatment as a usual arm. The allocation rate for all comparisons is 1:1. The effectiveness trial comprises a pre-treatment, during treatment, end of treatment, and follow-up design.

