#### Intervention description {11a}

##### Components of ITT

ITT is a 3-week intensive trauma treatment program and contains a preparation phase in week 1 and an intensive phase in weeks 2 and 3.

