##### Components of TAU

TAU is comparable across the four trauma centres and consists of low-frequent trauma-focused therapy with parenting therapy and family sessions. In contrast to the high intensity of FITT, TAU is offered about once a week and without therapist rotation. In TAU, the adolescents receive therapy from one therapist and parents receive therapy from another therapist. This individual or group-based trauma-focused cognitive behavioural therapy for adolescents and their parents is focused on the following components:
Psycho-education trauma and PTSD: increasing knowledge about (the consequences of) trauma and family violence and trauma-sensitive parenting and understanding the window of toleranceAffect regulation and coping: learning children to recognize and regulate feelings of stress and enhancing coping skillsTrauma processing: EMDR, exposure, writing therapy, or bodily oriented therapyParenting skills and competence: enhancing trauma-sensitive parenting skills, lowering levels of parental stress, and increasing social support.On indication: family relationships—sharing the trauma narrative and accompanying feelings and cognitions (for example feelings of shame or guilt) and strengthening of skills to prevent escalations

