Descriptive and exploratory analyses will be carried out by standard methods. All continuous scores will be examined for normality. If variable distributions deviate too much from normality, corrective steps will be taken either by transforming variables or by using non-parametric tests. We will control for child functioning, parental psychopathology, duration, severity, and intensity of interparental violence, and new IPV incidents. The variables are treated as covariables in the analyses mentioned below.

To examine our primary hypothesis, linear mixed models will be used in case of continuous data. GEE will be used for the categorical data. We will use the end of treatment (T12/T14) and intermediate/follow-up time-point (T13) to compare FITT with ITT (objective 1).

To examine our secondary hypotheses, linear mixed models will be used. We will use the end of treatment time-point (T12/T14) to compare FITT with TAU. Control measures are child functioning; parental psychopathology; duration, severity, and intensity of interparental violence; and new IPV incidents. The variables are treated as covariables in the up-mentioned analyses. We will use the Benjamini-Hochberg method to correct for multiple comparisons.

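### The FITT-TAU superiority question is set at 4 weeks, but the analysis section names only end of treatment (T12/T14) for that comparison

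*Protocol article*

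**What the plan says.** The FITT-TAU comparison is described in several places in the protocol article.

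- **Objectives {7}** asks: "After 4 weeks of treatment, does intensive trauma therapy for children with a family-based component (FITT) lead to a stronger reduction of trauma symptoms" than TAU. A separate question asks whether, once treatment has ended, FITT will "lead to an equal reduction of trauma symptoms and an equal increase of structural emotional safety" as TAU.
- **Trial design {8}** states: "This study is a superiority trial comparing FITT and TAU after 4 weeks of treatment". It places the FITT-TAU equivalence comparison at follow-up.
- **Explanation for the choice of comparators {6b}** wants to know whether FITT matches TAU at end of treatment and whether it works faster, and stresses the importance of the latter.
- **Sample size {14}** sizes the speed objective on two measurements: baseline and one labelled intermediate/follow-up.
- **Statistical methods {20a}** states: "We will use the end of treatment time-point (T12/T14) to compare FITT with TAU". T13 appears only as the "intermediate/follow-up time-point (T13) to compare FITT with ITT (objective 1").
- **Methods for additional analyses {20b}** plans none.

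On timing, Table 2 puts the last phase of FITT in week 4. For the comparator, "TAU is offered about once a week and without therapist rotation", and its total length is not given. Table 3 has one column headed T12/14. It lists CRIES at T0, T1-11, T12/14 and T13, and the emotional-security scales (SIS, SIFS, SIM-PR, Security scales) at T0, T12/14 and T13 only.

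**The concern.** The question that was designed and powered is about speed: how far each arm has come at a common early time. The only FITT-TAU comparison in the analysis section is made at end of treatment. If end of treatment means each arm's own finish, a faster treatment that arrives at the same place shows no advantage. The reverse error is also possible: an arm that simply had longer to recover can look better. In either case the trial could complete as planned and report a FITT-TAU result that does not answer its first secondary objective.

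The later comparison is unsettled too. Objectives {7} and the comparator rationale put equality at end of treatment, Trial design {8} puts equivalence at follow-up, and the analysis section does not assign T13 to FITT-TAU.

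**Working it through.** **1. The plan's own figure.** Inputs from Sample size {14}: f = 0.18, two groups, m = 2 measurements, correlation 0.5, non-sphericity correction 1, two-sided 5%, power 80%. For the group-by-time interaction, λ = N·f²·m/(1 − ρ).

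- N = 64: λ = 64 × 0.0324 × 2/0.5 = 8.29, power 0.809.
- N = 62: λ = 8.04, power 0.796.

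The smallest even N is 64, as stated. That is 32 per arm, 3 × 32 = 96 completers, and 96/0.80 = 120 randomised. At ρ = 0.5, f = 0.18 equals a difference in change of 4 × 0.18 = 0.72 SD. The sample size is sound; the issue is which time point it is spent on.

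**2. Time points side by side.**

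| Section | Superiority / speed | Equality / equivalence |
|---|---|---|
| Objectives {7} | 4 weeks | after end of treatment |
| Comparators {6b} | faster, no time given | end of treatment |
| Trial design {8} | 4 weeks | follow-up |
| Sample size {14} | baseline and intermediate/follow-up | none |
| Statistical methods {20a} | none named | end of treatment (T12/T14), not labelled as equivalence |

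The superiority column has no entry in the analysis section.

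**3. What an end-of-treatment comparison would show.** This step rests on assumptions that are not in the document: T12/T14 is each arm's own end of treatment; FITT reaches its gain by week 4; TAU changes linearly over W weeks; SD of change is 1; 32 per arm. W is unknown, so 8, 12 and 16 are shown. Write G_F and G_T for the final gains.

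- Week-4 contrast = G_F − G_T × 4/W.
- End-of-treatment contrast = G_F − G_T.
- The second falls short of the first by G_T × (1 − 4/W).

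*Equal final gain of 1 SD:*

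| W | Week-4 difference | Power at week 4 | End-of-treatment difference |
|---|---|---|---|
| 8 | 0.50 | 0.52 | 0 |
| 12 | 0.67 | 0.76 | 0 |
| 16 | 0.75 | 0.85 | 0 |

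The end-of-treatment test then rejects only at its 5% error rate. With a final gain of 0.8 SD the week-4 differences are 0.40, 0.53 and 0.60. With 1.2 SD they are 0.60, 0.80 and 0.90. (Power here uses the normal approximation, which gives 0.82 for the planned 0.72 SD.)

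*Equal weekly rate of 0.05 SD in both arms, so no difference in speed:* the end-of-treatment difference is 0.05 × (W − 4) = 0.2, 0.4 or 0.6 SD in favour of TAU from elapsed time alone, with rejection probability 0.12, 0.36 or 0.67.

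**The case against.** The strongest reply is that the end-of-treatment sentence is not wrong. It matches the equality question in Objectives {7} and the comparator rationale. That stands: the fault is an omitted time point for the other question. It also means that reducing T12/T14 to a descriptive role, or forcing T13 to one calendar distance from randomisation, would damage comparisons the protocol does promise.

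A second reply is that T12 may already be a week-4 visit, with T14 as the later end of TAU. T14 is numbered after T13, FITT itself finishes in week 4, and the participant timeline figure was not available in the text reviewed. This cannot be excluded. Against it, the analysis section treats T12/T14 as a single end-of-treatment time-point and uses the same label for FITT against ITT. Even on this reading, the week-4 FITT-TAU test is not named.

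Some stronger readings are tempting but unsupported:

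- A reader might take each arm's visit week as given. The treatment descriptions give programme content, not assessment dates, and TAU's length is never stated. That it exceeds 4 weeks is implied by asking separate 4-week and end-of-treatment questions.
- A reader might infer from Table 4 that T12 and T14 are one visit per family, or that the CRIES in-treatment series is collapsed. Table 4 appears to count the columns of Table 3: CRIES gets 4 despite T1-11. It also gives CAPS-CA 3, although Table 3 marks only two. It settles neither point.
- A reader might say the trial cannot test speed. That is true of a comparison at T12/T14, but CRIES is collected during treatment and could support the test.
- A reader might extend the point to FITT against ITT, because "ITT is a 3-week intensive trauma treatment program". FITT's extra week is the family-therapy phase, part of the component under test, and that comparison also uses T13.

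**Conclusion.** The concern holds as an inconsistency in the stated text. The 4-week superiority question in Objectives {7} and Trial design {8}, for which Sample size {14} requires 64 children, has no matching test in the analysis section. The equality question is placed at end of treatment in two sections and at follow-up in a third. This conclusion needs no assumption about visit dates.

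The numerical consequence is conditional. It requires T12/T14 to be arm-specific and TAU to last longer than 4 weeks. The zero at end of treatment follows directly from assuming equal final gains, so it illustrates the problem and does not estimate a bias. What does not depend on equal gains is the shortfall G_T × (1 − 4/W), which is half to three quarters of TAU's total gain for TAU lasting 8 to 16 weeks under linear change. The primary FITT-ITT comparison and the sample size are unaffected.

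**What to change.** 1. Define T12, T13 and T14 for each arm in weeks since randomisation.
2. Name the superiority test: a FITT-TAU contrast at week 4 from one linear mixed model on all CRIES records (T0, T1-11, T12/14, T13), using actual time since randomisation. Objectives {7} counts weeks of treatment, so state that randomisation is the clock. The spacing of T1-11 is not given; confirm that the TAU records cover week 4.
3. Keep the FITT-TAU comparisons at end of treatment and at follow-up for the equivalence question. Reconcile Objectives {7}, the comparator rationale {6b}, Trial design {8}, Sample size {14} and Statistical methods {20a} on which of the two is the test.
4. The objective also covers emotional safety, but those scales are not collected in T1-11. Either limit the week-4 claim to trauma symptoms or, if T12 is not already a week-4 visit in TAU, add a short week-4 round of those scales.

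Items 1 to 3 cost wording only, since CRIES is already scheduled during treatment. For item 4, Table 3's item counts give 43 + 7 + 15 = 65 child items and 28 + 15 = 43 parent items, against 232 and 335 for a full round.

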#### Sample size {14}

Power analysis was conducted to determine whether an informative trial could be conducted given limitations imposed upon the maximum sample due to the duration of the study and size of the population of children indicated for trauma treatment, using G*power 3 [95]. Sample size calculation was made based on the assumptions of the primary objective and the first secondary objective. A priori, we decided that adding systemic intervention elements to individual trauma therapy would be justified if it would mean that on average at least one out of five children would have clinically significant benefit when given the full FITT compared to treatment without systemic elements (number needed to treat = 5; equivalent to *f* = 0.18).

For primary objective 1 (Does intensive trauma therapy with a family-based component (FITT) lead to a stronger reduction of trauma symptoms and stronger increase of structural emotional safety than intensive trauma therapy without this family-based component (ITT)?), the sample size was calculated based on between 2 groups by within effect with at least two measurements (pre, end/follow-up), setting *f* = 0.18 with a power of 80% and a significance level of 5% (two-sided). Default settings were used for the correlation among repeated measures (= 0.5) and non-sphericity correction (*ε* = 1). According to the power analysis, a total sample size of 64 children is required.

Secondary objective 1 (Does intensive trauma therapy with a family-based component (FITT) lead to faster reduction of trauma symptoms and increase of structural emotional safety than low-frequency trauma treatment with parent therapy and family sessions?) is based on two measurements (pre and intermediate/follow-up). In accordance with the first sample size calculation, we tested with setting *f* = 0.18 with a power of 80%, a significance level of 5% (two-sided) was used. Again, default settings were used for correlation among repeated measures (= 0.5) and non-sphericity correction (*ε* = 1). Based on this calculation, a total sample size of 64 children is required.

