### Data collection and management

#### Plans for assessment and collection of outcomes {18a}

The instruments with the best psychometric qualities and sensitivity to change in a short time period are selected for this study. For the primary outcomes different types of measurements are included: questionnaires for multiple informants, an interview and an observation task. A description of the study instruments can be found in the “Outcomes {12}” section. For this study, researchers will be trained and certified in the CAPS-CA interview and scoring protocol. The researchers will write a report based on the interview part of the CAPS-CA, and other answers are entered in a SPSS file. All data collected by questionnaires will be collected through an online survey system, Survalyzer, minimizing entry errors. Data will be stored and coded in a SPSS file. The FIT observation tasks will be administered according to a protocol and the recoded tasks will be coded by trained researchers with the use of a standard scoring form. For both the CAPS-CA and the FIT observation task, inter-rater reliability will be calculated for 20 participants. All data will be cleaned before analyses (e.g. checking on double entries, ranges, checking dates of data collections with treatment dates, coding missing data) in IBM SPSS.

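### No instrument or time point is named as answering the primary question, yet the stated 80% power belongs to a single test at an unadjusted 5%

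*Protocol article*

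**What the plan says.** The primary objective (Objectives {7}) asks whether FITT, compared with ITT, will "lead to a stronger reduction of trauma symptoms of children and a stronger increase of structural emotional safety". That is two constructs in one question.

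Under Primary outcomes, Outcomes {12} describes three child PTSD instruments (CAPS-CA, CRIES, TSCC) and ten for security and safety (CTS, CTS-pc, PRTI, ACE-Q, new IPV incidents, SIS, SIFS, the parent-reported SIMS/SIM-PR, Security Scale, FIT). The plural is deliberate. Section {18a} says: "For the primary outcomes different types of measurements are included: questionnaires for multiple informants, an interview and an observation task". Table 4 gives each of the thirteen its own analysis row.

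Statistical methods {20a} compares FITT with ITT at end of treatment (T12/T14) and at T13. The paragraph on the secondary hypotheses then ends: "We will use the Benjamini-Hochberg method to correct for multiple comparisons". No family of tests is attached to that sentence.

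Sample size {14} sets the effect at f = 0.18 ("number needed to treat = 5; equivalent to" that value), "with a power of 80% and a significance level of 5% (two-sided"). The model is described thus: "the sample size was calculated based on between 2 groups by within effect with at least two measurements (pre, end/follow-up"). The conclusion is: "According to the power analysis, a total sample size of 64 children is required". The 20% inflation to 120 is for loss to follow-up and measurement unreliability only.

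**The concern.** A power statement means something only for a defined test. Here the sample size section powers one group-by-time contrast at 5%, while the outcome and analysis sections define a primary analysis with many contrasts and do not say which one, or which combination, answers the question. The power section leaves the time point open as well, since its second measurement may be end of treatment or follow-up.

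Two things are at stake. The first is the error rate of a primary claim. Benjamini-Hochberg limits the expected share of false findings among those declared. Once some effects are real, it does not hold the chance of any false finding at 5%. The second is power. A correction across many primary tests lowers the power for each of them below the stated figure. If there is no such correction, the 5% in the power statement applies to each test and not to the primary question.

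**Working it through.** **1. Reproduce the plan's figure.** Inputs from Sample size {14}: f = 0.18, two groups, two measurements (m = 2), correlation 0.5, ε = 1, two-sided 5%. For the within-between interaction, λ = f²·N·m/(1 − ρ) = 0.0324 × 64 × 2/0.5 = 8.29, with 1 and N − 2 = 62 degrees of freedom. Power from the noncentral F is 0.809 at N = 64 and 0.796 at N = 62, so 64 is right. That is 32 per arm, 96 over three arms, and 96/0.8 = 120. No step allows for multiplicity.

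**2. Count the FITT versus ITT tests** from Table 3, if each post-baseline time point is tested separately.
- All thirteen instruments: 11 at two time points, CAPS-CA at T13 only and FIT at T12/14 only: 22 + 1 + 1 = 24.
- Adding the second informant for CRIES, new IPV incidents and Security Scale: 24 + 3 × 2 = 30.
- Leaving out CTS, CTS-pc, PRTI, ACE-Q and new IPV incidents gives eight instruments: 6 × 2 + 1 + 1 = 14.
- One group-by-time test per instrument: 8 to 13.

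**3. Power and error if Benjamini-Hochberg covers these tests.** Assumptions that the protocol does not give: q = 0.05, equal correlation of 0 to 0.5 between test statistics, and every real effect of the planned size. I simulated 40,000 trials per setting, using a normal approximation with mean shift 1.960 + 0.875 = 2.835, which gives power 0.809 at 5%.

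| Tests | Power per outcome, one effect real | About half real | All real | Chance of any false claim, about half real |
|---|---|---|---|---|
| 8 | 0.55 | 0.67–0.69 | 0.76–0.78 | 0.07–0.09 |
| 13 | about 0.48 | 0.65–0.67 | 0.75–0.78 | 0.09–0.13 |
| 14 | 0.47 | 0.66–0.68 | 0.75–0.78 | 0.09–0.14 |
| 24 | 0.40–0.42 | 0.65–0.68 | 0.75–0.78 | 0.12–0.21 |
| 30 | 0.38–0.39 | 0.65–0.68 | 0.74–0.78 | 0.13–0.25 |

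When no effect is real, the chance of any false claim is about 0.04–0.05, as it should be.

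**4. If it does not cover them.** With every test at 5% and no real effect, the chance of at least one false positive is 1 − 0.95^k for independent tests: 0.51 for k = 14 and 0.79 for k = 30. At correlation 0.5, simulation gives about 0.35 and 0.51.

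**5. If both constructs must succeed**, each on one test at 5%, joint power is 0.809² = 0.65 under independence and at most 0.81 under perfect correlation.

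**The case against.** Four points can be made for the plan.

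**Scope of the correction.** The Benjamini-Hochberg sentence ends the secondary-hypotheses paragraph, so its reach to the primary tests is an inference. This stands, and the power loss in step 3 is conditional on it. The other reading leaves the primary tests uncorrected (step 4), so it does not rescue the plan.

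**The count.** The outcomes section calls the CTS, CTS-pc, PRTI and ACE-Q items a combined measure of violence exposure, and some items concern the parents' own childhood. The analysis section also uses violence severity and new incidents as covariates. A mixed model may give one test per instrument. These points stand, and are why the count is a range. Table 4 nevertheless lists the rows separately, and even eight tests leave power below 80%.

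**The size.** A reader might infer that power collapses to 35–38%. Those figures (0.353 at 0.05/30, 0.379 at 0.05/24) are the strictest, Bonferroni step. They approximate the case of one real effect among 24 to 30 tests, whereas the trial hypothesises broad benefit. If all effects are real, the loss is only a few points.

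**An unseen SAP.** The false discovery level, family and success rule may be set out there, so their absence is not the point. For the same reason, a reader may not conclude that success can be declared from any one of the tests, because the protocol states no such rule. What the article itself fixes is the list of primary outcomes, the time points and the basis of the power statement, and these do not fit together.

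False discovery rate control over several primary outcomes is also a recognised choice. It is defensible, but the power would then have to be stated for it.

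**Conclusion.** The point holds in a limited form. The sample size arithmetic is right, but the 80% belongs to one unadjusted test that the protocol does not identify. Under Benjamini-Hochberg the shortfall runs from a few percentage points (all effects real) to about 40 (one real among 30), depending on the number of real effects, the test count, q and the correlation, none of which the document settles. Without a correction for the primary tests, the stated 5% does not bound the chance of a false primary claim. Each reading leaves something to repair. The documents do not support the claim that power is 35–38%, or that Benjamini-Hochberg certainly governs the primary tests.

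**What to change.** Name one primary endpoint and one time point for FITT versus ITT, tested at two-sided 5% on a continuous scale, and state that the 80% power applies to that endpoint only. Follow it in fixed sequence with one named emotional-security scale. Make the other instruments secondary under Benjamini-Hochberg, and say which tests that family contains.

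CAPS-CA total severity at T13 is one candidate. Its Table 4 row would have to change, since it is now categorical, with GEE and three time points, while Table 3 shows CAPS-CA at T0 and T13 only. The outcomes section also gives the interview's age range as 8–18, while eligibility runs to 20, so that needs squaring too.

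If the team prefers two co-primaries at 2.5% each, power should be restated as about 72% at N = 64. Recovering 80% takes 76 per comparison, that is 38 per arm. With 20% loss this is 38/0.8 = 47.5, so 48 per arm and 144 in all.

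The single-endpoint route costs wording only, and 64 and 120 stand. Its price is that the other instruments can no longer support a primary claim.
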